
**Figure 3 F3:**
[figure not shown]
**Examples of C-Mill gait adaptability exercises.** Participants practice visually guided stepping to a sequence of regular or irregular stepping targets (**A**), obstacle avoidance (**B**), speeding up and slowing down by maintaining position in a moving walking zone (**C**), and all of the above in a functional and interactive gait adaptability game (**D**).

Note that we predict that the intensity of training, in terms of number of performed steps, will be markedly higher for both treadmill training intervention groups (i.e., AT and CT) than for the UC control group. We will test this prediction by comparing the number of steps taken per session among groups. To this end, the number of steps taken during AT and CT training sessions will be registered using the treadmill’s step counter while an observer will count the number of steps taken during UC sessions in a random sample of participants. We expect a main effect of Group in a one-way ANOVA, with post-hoc independent *t*-tests revealing significantly fewer steps for the UC control group than for both AT and CT training groups, in the absence of a significant difference between the latter groups.

To assist the therapist in progressively scaling the AT and CT training sessions, the participant’s perceived rate of fear and difficulty during AT and CT sessions will be assessed at a scale from 0 (no fear/not difficult) to 10 (much fear/very difficult), as well as their perceived rate of exertion using the 15 grade Borg scale (range 6-20, [37]).

Finally, adherence will be reported and the content of all individual training sessions will be registered by the supervising physical therapist. Adverse events during training sessions will be reported as well, and after completing the last UC, CT or AT therapy session of the intervention period, participants will fill out a purpose-designed questionnaire to register perceived discomforts during and after training sessions. The participant’s experience with the therapy program will be evaluated with this questionnaire as well to be able to compare the feasibility of the interventions from a participant’s perspective.

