### Data analyses

Descriptive statistics will be used to present group characteristics (e.g., sex, age, MMSE, medication use, comorbidities, side of fracture and the use of an assistive device), therapy adherence and adverse events. Baseline characteristics will be compared between groups with one-way ANOVAs. Given the explanatory objective of this study regarding the efficacy of C-Mill gait adaptability training, data will be analyzed per protocol, which implies that we will only include data of participants who completed at least 4 weeks of training and pre-intervention and post-intervention assessments (i.e., both T0 and T1). For longitudinal outcome measures (FAC, POMA, EMS, VAS, FES-I, TMT, NEADL, 10MWT, 10MWT_cognitive_, 10MWT_obstacle_, TUG, HOOS), multilevel regression analyses will be applied, which is appropriate for analyzing longitudinal data in which observations within one participant over time are correlated [61]. In addition, multilevel regression analyses account for missing values and allow baseline covariates to control for potential differences in baseline characteristics between groups [61].

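### The discomfort questionnaire used to compare feasibility is given after the last session of the intervention period, with nothing stated for those who stop early, so that comparison may understate discomfort

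*Protocol article*

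**What the plan says.** The relevant text is in the closing paragraphs of the Intervention program section of the protocol article.

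- **Timing.** The form comes once: "after completing the last UC, CT or AT therapy session of the intervention period, participants will fill out a purpose-designed questionnaire". The same section sets the intervention period at six weeks.
- **Content and use.** The form serves "to register perceived discomforts during and after training sessions" and also asks about the participant's experience of the programme, "to be able to compare the feasibility of the interventions from a participant’s perspective".
- **Other records.** "Adverse events during training sessions will be reported as well". Adherence is reported, and the therapist logs what was done in each session. In the two treadmill arms, "the participant’s perceived rate of fear and difficulty during AT and CT sessions will be assessed at a scale from 0", "as well as their perceived rate of exertion using the 15 grade Borg scale". The stated purpose of those ratings is "To assist the therapist in progressively scaling the AT and CT training sessions".
- **Non-adherent participants.** The Sample size section says that they are replaced, so that 126 people with four or more weeks of intervention and both T0 and T1 are obtained.
- **Analysis.** Data analyses lists "therapy adherence and adverse events" among the items to be described. Later in the same paragraph it restricts included data to participants with four or more weeks of training and both assessments. It names no separate set for safety or adherence.

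**The concern.** Someone who leaves the programme in, say, week 2 does not reach the point at which the form is handed out. If discomfort or fear is among the reasons for leaving, the people with most to report are the ones without a form. The feasibility comparison is then made among those who tolerated their programme. An arm that loses its least tolerant participants can look as acceptable as an arm that keeps them.

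Differential stopping is plausible, though not shown. AT exercises become harder from week to week, CT moves towards faster and longer walking, and UC has no treadmill component. What participants felt after sessions cannot be reliably recovered once they have left.

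**Working it through.** **1. The plan's own figures.** The article gives no rate for stopping during training and none for discomfort. Its one drop-out figure, 24%, covers T1 to T3. It agrees with the sample size (126/3 = 42 per arm; 1 − 32/42 = 23.8%), but it describes the time after training and does not estimate stopping during it.

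**2. What each record can show for an early stopper.**

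| Record | Depends on reaching the last session? | All three arms? | Participant's own report? | Covers time after sessions? |
|---|---|---|---|---|
| Questionnaire | Yes, on the natural reading | Yes | Yes | Yes |
| Adverse events | No | Yes | Not stated | No, tied to training sessions |
| Adherence, session content | No | Yes | Content is logged by the therapist | No |
| Fear, difficulty, exertion | No | AT and CT only | Yes | No |

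An early stopper therefore leaves some trace. None of the other records gives participant-reported discomfort in all three arms, including after sessions.

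**3. Overlap with the analysis set.** The inclusion rule admits people with four or five of the six weeks. If the form is given only at the end of six weeks, some participants in the per-protocol set may have no form either.

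**4. Level within one arm.** Let c be the proportion with notable discomfort among finishers, s the proportion among early stoppers, and f the fraction stopping early. All three are assumptions.

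True proportion = c(1 − f) + s·f. The form shows c. Understatement = f(s − c).

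| c | f | s | True | Understatement (points) |
|---|---|---|---|---|
| 10% | 5% | 50% | 12.0% | 2.0 |
| 10% | 5% | 100% | 14.5% | 4.5 |
| 10% | 20% | 50% | 18.0% | 8.0 |
| 10% | 20% | 100% | 28.0% | 18.0 |
| 30% | 5% | 50% | 31.0% | 1.0 |
| 30% | 24% | 100% | 46.8% | 16.8 |

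The sign depends on s exceeding c. If people stop for reasons unrelated to discomfort and s = c, nothing is lost.

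**5. Contrast between two arms.** Take c = 30% in both arms, so the forms show no difference. With s = 80% in both, the hidden difference is (f₁ − f₂)(0.80 − 0.30).

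- 10% v 10% stopping: 0 × 0.50 = 0 points
- 20% v 10%: 0.10 × 0.50 = 5 points
- 24% v 5%: 0.19 × 0.50 = 9.5 points

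With equal stopping of 10% but s = 80% in one arm and 50% in the other, the hidden difference is 0.10 × (0.80 − 0.50) = 3 points. The contrast is therefore distorted only when stopping, or discomfort among stoppers, differs by arm.

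**6. Adherence and adverse-event summaries.** Two readings of Data analyses are open. The four-week rule is worded without exception, in the same paragraph as the descriptive summaries. On that reading, an event that ended training in week 2 would not be tabulated. However, the rule follows the sentence on descriptive summaries and is justified by the efficacy objective, and the Intervention program section promises adverse-event reporting without limiting it to any set. The text does not settle which reading is meant.

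**The case against.** The strongest reply has five parts.

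- **Other records exist.** A reader might infer that the form is the only record of tolerability. The documents do not support that: adverse events, adherence and session content, and in AT and CT the fear, difficulty and exertion ratings, do not require reaching the last session. This stands, and it limits the gap to participant-reported discomfort across all arms and after sessions.
- **Bias is not established.** A reader might infer that the comparison must favour the treadmill arms. The form is used in all three arms, UC can lose people too, and no rates are given. This also stands: bias in the contrast is conditional.
- **The four-week rule may not reach safety data.** It might be inferred that early adverse events are dropped, or that adherence has a floor. The text ties the rule to neither. A floor also depends on an undefined metric: 4/6 = 67% of weeks, but 2 + 2 + 2 + 3 = 9 of 15 treadmill sessions, or 60%, and missed sessions could lower it further. What stands is a question of scope.
- **The wording is open, and an article condenses.** The last session could mean each participant's own last one, and the handling of withdrawals may be in the full protocol. This lowers the weight of the point. It does not remove it, because the article itself states both the timing and the comparison that rests on it.
- **The consequence is small.** The form is not among the primary or secondary outcomes, and no test or sample size depends on it. This stands.

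**Conclusion.** The concern holds in limited form and is minor. As written, the feasibility comparison from the participant's perspective rests on a form with no stated completion for early stoppers, while the plan expects non-adherent participants and replaces them. If stoppers had more discomfort than finishers, each arm's level is understated. Under the assumed inputs the understatement is 1 to 18 percentage points across the two starting rates. If stopping or discomfort among stoppers differs by arm, the contrast is biased as well: 3 to 9.5 points in the unequal examples, and none when both are equal. These sizes illustrate the mechanism and are not estimates for this trial.

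Whether the four-week rule governs adherence and adverse events is unclear and should be stated. The primary and secondary outcomes are not touched by this point.

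**What to change.** Make two changes of one sentence each.

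1. **Procedures (Intervention program).** State that the same questionnaire is completed at each participant's last attended session, whenever that falls, and that the reason for stopping is recorded for anyone who leaves early. This also settles which last session is meant.
2. **Reporting (Data analyses).** State that questionnaire results, adherence and adverse events are summarised by allocated arm for everyone who started at least one session, including those later replaced, with the questionnaire response rate per arm. The four-week rule then clearly does not govern these summaries.

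No new instrument is needed, and the sample size is unchanged. The cost is some follow-up of people as they leave. Some early stoppers will decline, so the gap will narrow but not close, which is why response rates per arm must be shown beside the results.

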### Outcome measures

Measures related to walking ability are the primary outcome in this study, whereas measures related to fear of falling, fall incidence and general health are secondary outcomes. Table 1 provides an overview of the assessments performed at T0, T1, T2 and T3.

**Table 1 T1:** Study assessment schedule

		**Intake**	**T0**	**T1**	**T2**	**T3**

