**Methods/design:**

The protocol describes a parallel group, single-blind, superiority randomized controlled trial with pre-tests, post-tests, retention-tests and follow-up. Hundred-twenty-six older adults with a recent fall-related hip fracture will be recruited from inpatient rehabilitation care and allocated to six weeks of C-Mill gait adaptability treadmill training (high-intensity, adaptive stepping), conventional treadmill training (high-intensity, repetitive stepping) or usual care physical therapy using block randomization, with allocation concealment by opaque sequentially numbered envelopes. Only data collectors are blind to group allocation. Study parameters related to walking ability will be assessed as primary outcome pre-training, post-training, after 4 weeks retention and 12 months follow-up. Secondary study parameters are measures related to fall incidence, fear of falling and general health.

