### Study design

This protocol presents a parallel group, single-blind, superiority randomized controlled trial with pre-tests, post-tests, retention-tests and follow-up (Figure 2) to evaluate the relative efficacy of three intervention programs. Prior to randomization, pre-intervention assessments (T0) will be performed by one of two assessors within one week from informed consent. Subsequently, the assessor will randomly allocate (ratio 1:1:1) participants to one of three groups: 1) usual care (UC) control group, 2) conventional treadmill (CT) intervention group, 3) adaptability treadmill (AT) intervention group. We will use computer-generated block randomization with a block size of 21 participants to ensure equal group size after each block, with allocation concealment by opaque sequentially numbered envelopes that will be allocated serially to participants. An independent assessor blinded to group allocation will conduct post-intervention assessments (T1) within one week after completion of the intervention program. The same assessor will repeat these assessments 1 month later (retention assessments, T2). Follow-up assessments (T3) will be performed 12 months after completion of the intervention program. Furthermore, the incidence of trips, slips and falls will be monitored monthly between T1 and T3.

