**Primary outcome measures related to walking ability**						
Performance Oriented Mobility Assessment (POMA)			x	x	x	x
10 Meter Walking Test with obstacles (10MWT_obstacle_)				x	x	
10 Meter Walking Test with cognitive task (10MWT_cognitive_)				x	x	
Trail Making Test (TMT)			x	x	x	x
Functional Ambulation Category (FAC)		x	x	x	x	x
Elderly Mobility Scale (EMS)			x	x	x	x
10 Meter Walking Test (10MWT)				x	x	
Timed Up-and-Go test (TUG)				x	x	
Nottingham Extended Activities of Daily Living (NEADL)			x		x	x

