### Sample size

We used the POMA [38] to perform a sample size calculation, because the POMA is a generic and widely used test to evaluate walking ability and has been associated with risk of falling [39,40]. Earlier clinical trials in which the POMA was used as an outcome measure reported mean differences of 4.0 and 3.5 POMA points between the intervention and control group [59,60]. The average standard deviations at follow-up measurements in these studies were respectively 3.8 and 4.8 POMA points. Assuming the lowest difference in mean value between groups (i.e., 3.5 POMA points), the highest standard deviation (i.e., 4.8 POMA points) and a correlation coefficient of 0.7, a sample size of 32 participants in each group is required to achieve 80% power with a two-tailed conservative alpha of 0.017 that is corrected for multiple comparisons. This sample size is based on the formula given by Twisk [61] to compare longitudinal outcome measures between groups.

We will include 126 participants who complete at least four weeks of intervention and pre- and post-intervention assessments (i.e., T0 and T1). Hence, participants who do not adhere to the protocol will be replaced to maintain a valid per-protocol assessment of sufficient power. In addition, this sample size allows for a maximum drop-out rate of 24% from T1 to T3.

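### Nine unranked measures are labelled primary, while the alpha of 0.017 and the sample size fit a single outcome (POMA) with three group contrasts

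*Protocol article*

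**What the plan says.** All references are to the protocol article.

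- **Outcome measures:** "Measures related to walking ability are the primary outcome in this study". The label is attached to a group of measures, not to one of them.
- **Table 1:** under "Primary outcome measures related to walking ability" it lists nine: POMA, 10MWT with obstacles, 10MWT with cognitive task, TMT, FAC, EMS, 10MWT, TUG and NEADL.
- **Abstract, Methods/design:** "Study parameters related to walking ability will be assessed as primary outcome pre-training, post-training, after 4 weeks retention and 12 months follow-up". This is again plural and unranked.
- **Study design:** "the assessor will randomly allocate (ratio 1:1:1) participants to one of three groups", which gives three pairwise contrasts: AT versus UC, CT versus UC and AT versus CT.
- **Sample size:** the calculation is done on POMA, chosen as a generic and widely used test, and aims for "80% power with a two-tailed conservative alpha of 0.017 that is corrected for multiple comparisons". POMA is not called the primary outcome here or elsewhere.
- **Data analyses:** twelve longitudinal measures, the nine primary ones and three secondary ones, get the same type of multilevel regression. No lead measure, order of testing or adjustment across measures is given.

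**The concern.** A primary outcome is meant to fix in advance which result decides the main question. Here nine results carry that status equally, and nothing says whether the trial succeeds on one, on most or on all of them. The one multiplicity correction has the size needed for three group contrasts on one outcome, and the power calculation also concerns one outcome. The primary label is therefore wider than the error control and the power behind it.

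At stake is how the main conclusion will be read. With nine measures of equal rank, an isolated significant difference on any of them could be reported as a primary finding at an alpha described as conservative, although that alpha was not set for nine measures.

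The measures also differ in how well they can carry a primary claim. TUG and the three 10MWT versions have no T0 value, and the Limitations section itself asks for caution with results on such measures. They nevertheless have the same status as POMA.

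**Working it through.** **1. Reproduce the plan's sample size.** Inputs from Sample size: difference 3.5, SD 4.8, correlation 0.7, two-sided alpha 0.017, power 80%. The number of follow-up measurements, T, is not stated. T = 3 is inferred; Table 1 schedules POMA at T1, T2 and T3.

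n = 2 × (z for alpha + z for power)² × SD² × [1 + (T − 1) × ρ] / (T × difference²)

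- Without the longitudinal factor: 2 × (2.387 + 0.842)² × 4.8² / 3.5² = 39.2.
- Longitudinal factor: (1 + 2 × 0.7) / 3 = 0.8.
- n = 39.2 × 0.8 = 31.4, so 32 per group.

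This matches the plan ("a sample size of 32 participants in each group is required to achieve 80% power"). The drop-out allowance also fits: 126 / 3 = 42, and 42 × 0.76 = 31.9. The sample size is not in error.

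**2. What 0.017 covers.** The text says only that it corrects for multiple comparisons. Candidate divisors:

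- three contrasts: 0.05 / 3 = 0.0167, which fits;
- nine measures: 0.05 / 9 = 0.0056, which does not fit;
- nine measures × three contrasts: 0.05 / 27 = 0.0019, which does not fit.

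The reading as three contrasts on one outcome is inferred, but it is the only one of the three that agrees with the figure.

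**3. Error rate if any of the nine counted.** Simulation with no true effect: three equal groups, nine equicorrelated measures, one longitudinal test per measure and contrast (9 × 3 = 27), each two-sided at 0.017 (|z| > 2.387), 200,000 runs. The dependence between the three contrasts is built in. The between-measure correlation is an assumption. The 0.7 in the Sample size section is taken as the correlation between repeated measurements of one outcome, so it does not supply this value.

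| Between-measure correlation | At least one false difference, either direction | Favourable direction only (AT > CT, AT > UC, CT > UC) |
|---|---|---|
| 0 | 33.8% | 19.2% |
| 0.3 | 30.3% | 16.6% |
| 0.5 | 25.3% | 13.8% |
| 0.7 | 19.3% | 10.6% |
| 0.8 | 15.8% | 8.5% |
| 0.9 | 11.6% | 6.2% |

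Reference for one outcome with three contrasts: about 4.5% in either direction (Bonferroni bound 3 × 0.017 = 5.1%). In the favourable direction the bound is 3 × 0.0085 = 2.55%.

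**4. What each remedy does to the design.**

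- *POMA alone, three contrasts at 0.017:* error about 4.5%, 32 per group unchanged.
- *All nine kept, Bonferroni over 27 tests (alpha 0.00185):* error 3.0% to 4.7% for correlations from 0.7 to 0. The same formula for POMA gives 47.1, so 48 per group and 3 × 48 = 144 evaluable, which exceeds the planned 126 before any drop-out. Power for POMA would be 56% at 32 per group and 73% at 42.

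**The case against.** The strongest reply is that the protocol nowhere says that one significant result among 27 counts as success. The 0.017 appears only as an input to the sample size, and Data analyses gives no threshold or success criterion. The procedure across outcomes is commonly left to an analysis plan, which may exist. This stands as far as it goes: the any-of-nine reading is a conditional, not a quoted rule. It does not remove the point, because the primary label on nine unranked measures is a choice that this document makes in the abstract, in the text and in Table 1. An analysis plan that named one primary outcome would depart from it.

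Four further readings are tempting, and the documents do not support them as stated.

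- *That the chance of a false success is 20% to 34%.* Those figures count differences in either direction, including usual care beating the treadmill groups. The hypotheses are directional, and the favourable-direction rates are roughly half as large. AT over CT is moreover hypothesised only for adaptability aspects. If that contrast is limited to the obstacle and cognitive 10MWT and the TMT, which is itself a reading of the text, the rate is about 15.5% at correlation 0, 11% at 0.5 and 9% at 0.7. A correlation of 0 is also implausible, since three of the nine are versions of one walking test and several others are mobility measures in the same people.
- *That repeated visits multiply the error further.* Both the sample-size formula and the planned models are longitudinal. No separate tests by visit are announced.
- *That TMT and NEADL do not belong.* The heading speaks of measures related to walking ability, and the Discussion gives a rationale for TMT.
- *That the explanatory aim excuses the lack of a lead outcome.* The trial is presented as a superiority trial with stated hypotheses and a corrected alpha, so a designated outcome is still needed.

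**Conclusion.** The point holds in limited form. Nine measures are labelled primary without rank or combination rule, while the only multiplicity correction and the only power calculation fit one outcome with three contrasts. If any of the nine were taken as decisive at 0.017, the two-sided error would be about 12% to 34%, and the favourable-direction error about 6% to 19%, for between-measure correlations from 0.9 down to 0. A single outcome gives about 4.5% two-sided.

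This rests on three assumptions: that 0.017 stands for 0.05/3; that each measure and contrast is tested once; and the correlation values, which the documents do not give.

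A reader might infer that the trial has no error control at all, or that its size is wrong. Neither follows: 0.017 does control the error for one outcome, and 32 per group reproduces for POMA. The weakness lies in the labelling. It should be fixed, and it can be fixed in the wording.

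**What to change.** In the abstract, in Outcome measures and in Table 1, name POMA as the single primary outcome. Analyse it longitudinally over T1, T2 and T3, in line with the sample-size calculation, with the three pairwise contrasts each tested at two-sided 0.017. Relabel the other eight walking-ability measures as secondary, and state in Data analyses that 0.017 refers to the three contrasts on POMA. T = 3 is inferred, so the number of follow-up measurements in the formula should be stated too.

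**Cost.** The 32 per group, the 126 in total and the data collection stay as they are. Eight measures lose primary status, among them the gait-adaptability measures, so the hypothesis that AT outperforms CT on adaptability becomes secondary.

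If the sponsor wants that hypothesis to be confirmatory, the protocol must name one adaptability measure in advance and say exactly which POMA contrast has to succeed before it is tested. The obstacle 10MWT is an obvious candidate, but it has no T0 value and falls under the caution in the Limitations section. The documents give no power for it.
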